#### Waitlist condition

Participants randomly allocated to the waitlist condition will not receive any therapeutic support from their assigned coach or the research team during the 8-week waiting period. Participants are asked not to take up psychological support during the waiting period (i.e. CBT, counselling) or change their current psychotropic medication if they are already taking it to allow for a clean comparison between conditions. If a participant wishes to access the SHAPE intervention, they will be able to receive the intervention after they complete their post-wait measures and have their second telephone assessment at 8 weeks post-random allocation. If a participant no longer wishes to receive the intervention, they can opt out and will be provided with relevant information on alternative services if requested.

### Criteria for discontinuing or modifying allocated intervention/comparator for a trial participant {15b}

We deem our trial to be low risk due to the nature of the intervention and the trial design. However, thoughts of death, suicidal ideation, and increased risky behaviours can be symptoms of MDD and PTSD. Risk will be carefully monitored throughout the trial through the questionnaires, the clinician-administered assessments, and from regular weekly contact with the coach for participants assigned to the intervention condition. All participants will be made aware of the study team’s contact details in the study information sheet should they need to be in touch regarding risk. A risk and safeguarding plan has been developed for the trial, and all coaches and assessors have been briefed on how to use it and the steps to take if a participant demonstrates signs of risk or if a safeguarding concern emerges.

#### Participants in the intervention condition

Some participants in the 8-week intervention condition might experience worsening of symptoms during this time. For some participants, an unexpected life event might occur whilst they are in the intervention condition. If this event causes severe distress and risk emerges, the study team will assess if a more urgent support service is required. If the study team deems that a participant would require a more urgent support service, the participant will be withdrawn from the study and referred to the relevant support service, with consent. If a participant needs to take some time off due to the unexpected life event, their intervention will be paused, and they will be able to resume coaching within 6 months after pausing or have the option to withdraw.

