#### Participants in the waitlist condition

Some participants in the 8-week waitlist condition might experience worsening of symptoms during this time due to the progression of symptoms or factors such as an unexpected life event. The study team will be able to detect this in the participant’s 4-week and 8-week questionnaires. The study team will contact the participant and conduct a risk assessment if they detect an increase in risk from baseline. If it is deemed that the participant would benefit from immediate assessment or treatment from a mental health service, then the study team will withdraw the participant from the trial and refer them to the relevant support service.

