### Adverse event reporting and harms {17}

Participant risk and safety will be monitored throughout the trial. A protocol for defining and recording serious adverse events (SAEs) and adverse events (AEs) has been developed for the trial that will be referred to throughout the trial (see Appendix 1). If a SAE or AE is reported from a participant, an AE or SAE report form (as appropriate) will be filled out by the safeguarding lead who is on-call and also sent to the PI to complete and review. Only SAEs will be reported to the TSC, unless an AE is recurring or has been reported more than once for a participant.

For participants assigned to the intervention condition, SAEs and AEs will be monitored through screening questionnaires, SCID-5 telephone assessments, weekly questionnaires, and during coaching calls. For participants assigned to the waitlist condition, SAEs and AEs will be monitored with the study questionnaires and SCID-5 telephone assessments at baseline, 4-week post-random allocation, and 8-week post-random allocation.

During SCID-5 telephone assessments, assessors will be asked to complete a brief risk assessment if a participant discloses suicidal ideation. After the assessment, assessors will be required to consult with the available safeguarding lead on the research team for guidance on what necessary action needs to be taken, and the PI will be informed. A SHAPE AE or SAE report form will be completed by the safeguarding lead (see Appendix 2) and PI (see Appendix 3) and safely stored in a secure online location on Nexus 365 OneDrive for Business.

During calls, coaches will be asked to notify the assigned safeguarding lead directly should they be concerned at any time that a participant has caused, or is likely to cause, significant harm to themselves or others. Coaches will conduct risk assessments if they deem a participant to be showing signs of risk during the call, or if item 9 on the PHQ-9 increases from their baseline value. If a participant is deemed to be at high risk, the study team will inform the participant’s GP with consent from the participant in order to ensure participant safety. If a coach is concerned that a participant is believed to likely cause imminent significant harm to others, they will need to pass this information onto the assigned safeguarding lead, who will be required to inform the appropriate authorities directly.

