## Methods: data collection, management, and analysis

### Plans for assessment and collection of trial data {25a}

Outcome data will be collected from all participants, including participants who withdraw from the intervention wherever possible. Furthermore, participants will be thanked with an honorarium of £20 once they complete their second SCID-5 assessment to improve data collection and completeness. In addition, for participants who withdraw or who are difficult to contact, multiple efforts will be made by the research team to reach these participants and invite them to complete measures at all data collection timepoints. Attempts will be made through different modalities (i.e. email, telephone, SMS) in case participants change contact information or are more accessible through one modality. The research team will continue to contact hard-to-reach participants throughout the trial until they complete outcome data or they withdraw consent from being sent outcome measure invitations. Shortened versions of questionnaires will also be made available to participants to complete, which will contain the most important measures (i.e. PCL-5 and PHQ-9) to reduce the potential burden on participants who struggle to complete follow-up measures. An additional monetary incentive (£10 e-voucher) for filling out a shortened questionnaire (PCL-5 and PHQ-9) will be issued for particularly hard-to-reach participants who do not respond to any contact method and who have not completed either the self-report measures or SCID-5 assessment at any post-randomisation timepoint. Most of the outcome data will be collected using Qualtrics [57], a widely used data collection online software programme. Participant outcome data on Qualtrics will be pseudonymised by participant ID. Access to the outcome data will be restricted to the main study team (JL, JW, CC, AE, and AM) using a secure login (two-factor authentication). To minimise data entry errors and ensure completeness, data validation procedures including force response settings and single-choice restrictions will be implemented within the Qualtrics survey platform where applicable. The only data that will not be collected over Qualtrics is the SCID-5 assessment measures collected at baseline, 8 weeks post-random allocation, and 6 months post-intervention completion as well as the semi-structured interviews. This data will be in the format of interview recordings, online SCID-5 assessment sheets, and online topic guides that will be safely stored in restricted access folders on Nexus 365 OneDrive for Business, only accessible by the main study team. Data completeness and anomalies will be checked on a weekly basis by the trial lead (JL), and any issues will be flagged and brought to weekly supervision with the PI (JW) to be resolved on a case-by-case basis.

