### Plans to promote participant retention and complete follow-up {25b}

To support retention and prevent dropouts, participants and prospective participants will receive a £10 e-voucher as an honorarium for each SCID-5 assessment they complete (4 assessments for the waitlist condition, 3 assessments for the intervention condition, and 1 assessment for prospective participants found to be ineligible). Participants will be able to spend their e-voucher on a variety of brands.

Participants are allowed to withdraw at any stage of the trial and ask for their data to be deleted. Their future treatment in NHS and private services will not be affected by withdrawing from the study. Withdrawal after randomisation will be recorded along with reasons (if provided). Participants who withdraw from the intervention or waitlist condition will continue to be sent follow-up questionnaires unless they withdraw their consent for this.

Participants who do not respond to initial invitations to take part in SCID-5 assessments will be contacted using a variety of available approaches (email, phone call, SMS) unless they have withdrawn their consent from the trial. Participants who are reluctant to complete the longer questionnaires or the SCID-5 assessments at 4 weeks post-random allocation, 8 weeks post-random allocation, or 6 months post-intervention completion will be sent the PCL-5 and PHQ-9 as a minimum dataset.

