#### Main trial analyses

##### Primary outcome

The primary outcome measure will be SCID-5 diagnosed PTSD and MDD at 8 weeks post-random allocation. The primary outcome measure will be analysed using logistic regression. The outcome will be a binary outcome measure whereby, if a participant meets diagnosis for one or both disorders (PTSD and/or MDD), they will score a 1 (present), whereas if a participant does not meet diagnostic criteria for either disorder, they will score a 0 (absent). All participants will begin the trial with a score of 1 since they will have a diagnosis of PTSD and/or MDD at the outset, consistent with eligibility criteria.

Where the primary outcome is measured at one time point, it has been shown that logistic regression is valid with a data missing at random assumption [66]. Complete case analysis will be conducted if missingness is <5%, whereby participants with missing data will be excluded from the primary analysis. Multiple imputation will be conducted as a sensitivity analysis for the primary outcome if missingness is >5% to check for robustness of results.

Models will include fixed factors of condition (SHAPE, waitlist). The stratification variables absence/presence of PTSD assessed with the SCID-5 at baseline, depression symptom severity (<15 or 15) assessed at baseline with the PHQ-9, and time since reported trauma (>/<18 months) assessed at baseline with the PCL-5 will be included as fixed covariates. The significance level will be set to *p* < 0.05 for comparison between the SHAPE and waitlist conditions.

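### Participants withdrawn because of risk leave the study, not only their condition, so the week-8 SCID-5 may be missing for people likely still to have a diagnosis

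*Protocol article*

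**What the plan says.** Two rules in the protocol article, under the criteria for discontinuing or modifying the allocated condition {15b}, take people out of the study:

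- **Intervention arm** (Participants in the intervention condition). The rule follows an unexpected life event: "If this event causes severe distress and risk emerges, the study team will assess if a more urgent support service is required". If the team concludes that it is, "the participant will be withdrawn from the study and referred to the relevant support service, with consent".
- **Waitlist arm** (Participants in the waitlist condition). If the 4-week or 8-week questionnaires show increased risk, a risk assessment follows. If the team judges that immediate assessment or treatment would help, "then the study team will withdraw the participant from the trial and refer them to the relevant support service".

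Other sections point towards continued follow-up:

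- The section on assessing and collecting trial data {25a} opens with this commitment: "Outcome data will be collected from all participants, including participants who withdraw from the intervention wherever possible". It adds that "for participants who withdraw or who are difficult to contact, multiple efforts will be made by the research team to reach these participants".
- Plans to promote participant retention {25b}: "Participants who withdraw from the intervention or waitlist condition will continue to be sent follow-up questionnaires unless they withdraw their consent for this".
- Statistical methods {27a and 27b}: all analyses are by intention to treat, whether or not follow-up is completed.

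The primary outcome is presence or absence of PTSD and MDD on the SCID-5 interview 8 weeks after randomisation. On missing values, the Primary outcome section under Main trial analyses says that "it has been shown that logistic regression is valid with a data missing at random assumption". Below 5% missing it plans a complete case analysis. Above 5% it adds multiple imputation. Section {27c} refers to the statistical analysis plan, which is not shown, for more on missing data.

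**The concern.** Section {15b} is about leaving an allocated condition, yet its wording takes the person out of the study. Staff who follow it literally could stop outcome collection for exactly those participants whose state has become alarming. Many of them would probably still meet criteria for PTSD or MDD at week 8. If their SCID-5 is missing, non-recovered people leave the denominator and recovery in that arm looks better than it was.

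The follow-up sections do not settle this. The first sentence of {25a} concerns people who withdraw from the intervention, and {25b} concerns people who withdraw from a condition. A withdrawal from the whole study, decided by the team, is neither of these, nor is it a withdrawal of consent. The express promise in {25b} is for questionnaires, with the PCL-5 and PHQ-9 as the minimum set, and questionnaires do not supply a SCID-5 diagnosis.

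The missing-data methods named in the article assume data missing at random. With few missing outcomes, no check on that assumption is named.

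**Working it through.** **Inputs.** From Sample size {19}: recovery 50% in SHAPE and 16% on the waitlist, 90% power, alpha 0.05 (taken as two-sided, because the sidedness is not stated), 39 per arm, and 46 per arm after 15% attrition. From Primary outcome (Main trial analyses): the 5% threshold. The numbers withdrawn are assumptions, because the article gives none.

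**Plan's own figure.** Two proportions, pooled variance under the null, no continuity correction:

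n = [1.960 × √(2 × 0.33 × 0.67) + 1.282 × √(0.50 × 0.50 + 0.16 × 0.84)]² / 0.34² = 38.1, so 39 per arm.

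39 / 0.85 = 45.9, so 46 per arm and 92 in total. The stated sample size reproduces.

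**What the 5% threshold means.** 4/92 = 4.3% and 5/92 = 5.4%. With up to 4 missing outcomes, complete case analysis is the only method that the article names.

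**Effect of losing non-recovered participants.** Expected recoveries are 0.50 × 46 = 23 in SHAPE and 0.16 × 46 = 7.36 on the waitlist. If w people who are not recovered are missing, the observed rate is recoveries / (46 − w).

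| Lost from SHAPE | Lost from waitlist | SHAPE rate | Waitlist rate | Difference (points) | Odds ratio |
|---|---|---|---|---|---|
| 0 | 0 | 23/46 = 50.0% | 7.36/46 = 16.0% | 34.0 | 5.25 |
| 2 | 2 | 23/44 = 52.3% | 7.36/44 = 16.7% | 35.5 | 5.45 |
| 4 | 0 | 23/42 = 54.8% | 16.0% | 38.8 | 6.36 |
| 0 | 4 | 50.0% | 7.36/42 = 17.5% | 32.5 | 4.71 |
| 2 | 4 | 52.3% | 17.5% | 34.7 | 5.15 |

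Each of the second, third and fourth rows loses 4 of 92, so each falls under the complete case rule.

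**Direction.** Within an arm, the observed recovery rate can only rise under this assumption. Between arms, the result depends on the balance of losses and on the scale. For small losses, one SHAPE loss moves its rate 0.50/0.16 = 3.1 times as far as one waitlist loss, so the difference shrinks only if waitlist losses are roughly three times those in SHAPE. On the odds ratio scale, which logistic regression uses, the balance point is lower. There are 23 non-recovered in SHAPE and 46 − 7.36 = 38.64 on the waitlist, and 38.64/23 = 1.68. The last row shows the two scales disagreeing: the difference is slightly above 34.0 while the odds ratio is below 5.25.

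**The case against.** Much can be said for the plan.

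- **The trigger is narrow.** Worsening of symptoms alone does not remove anyone. Both arms require a team judgement about urgent or immediate care, the intervention arm also offers a pause, and people with imminent, persistent, clinically significant risk are excluded at entry (Table 1). Such withdrawals may be few. This stands.
- **Follow-up of withdrawn people is planned.** The second statement quoted from {25a} refers to participants who withdraw, without limiting this to the intervention, and invites them to measures at all timepoints. Section {25b} pursues non-responders to SCID-5 invitations unless they have withdrawn consent. This stands far enough to make loss a risk and not a stated consequence. It does not remove the conflict with {15b}.
- **Informative is not the same as not at random.** Risk is picked up largely through recorded scores. If those scores enter the imputation model, missing at random may be reasonable. This stands for multiple imputation. The complete case analysis planned below 5% makes no use of later scores.
- **The analysis plan may add more.** It is not shown, so nobody can say from the article that no analysis would reveal the problem, and the absence of a delta-adjusted imputation is not a fault here.

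A reader might infer that the bias must favour SHAPE, because in that arm "SAEs and AEs will be monitored through screening questionnaires, SCID-5 telephone assessments, weekly questionnaires, and during coaching calls", while the waitlist is monitored mainly at weeks 4 and 8. The documents do not support that as a conclusion. The waitlist wording is arguably the lower bar (would benefit from care, as against would require it), has no pause option, and applies to people receiving no therapeutic support. Either arm could lose more.

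**Conclusion.** The point holds as an unreconciled conflict that puts some primary outcomes at risk. Section {15b} withdraws people from the study or trial. Sections {25a}, {25b} and {27a and 27b} require that they be followed and analysed. Only questionnaires are expressly promised to those who have left a condition.

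If those lost are not recovered, recovery in their arm is overstated by 2.3 points with 2 of 46 lost and by 4.8 points with 4 lost, from a true 50%. The treatment difference could read anywhere from 32.5 to 38.8 points against a true 34.0 with 4 participants lost in all. These sizes rest on assumed counts, on every lost participant being non-recovered, and on the planning rates being true. The documents establish neither that outcomes will be lost nor that the treatment effect will be overstated.

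**What to change.** Leave the referral decision and its criteria as they are.

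1. Reconcile {15b} with {25a}, {25b} and {27a and 27b}: state that a participant withdrawn because of risk leaves the allocated condition, remains in the intention-to-treat population, and is still invited to the week-8 SCID-5 unless consent to follow-up is withdrawn.
2. Whatever the percentage missing, name one sensitivity analysis of the primary outcome that scores a missing week-8 SCID-5 after a risk-triggered withdrawal as diagnosis present. Under the assumption used above, this restores 23/46 against 7.36/46, a difference of 34.0 points. Keep it as a sensitivity analysis: it would err the other way if some of these people had recovered, so making it the primary analysis would be a trade-off and not a plain gain.
3. Report, by arm, how many such withdrawals occurred and how many had a week-8 SCID-5. Reasons for withdrawal are already to be recorded under {25b}, where participants give them.

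Recruitment is complete and this version is dated October 2025, so new wording will recover few if any week-8 interviews. The sensitivity analysis is the part that can still change the week-8 result. Because {28b} plans an analysis once the 8-week data are in, date the addition and say whether results by arm had already been seen. The cost is a wording change, one extra analysis and possibly a less favourable recovery rate.

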#### Participants in the waitlist condition

Some participants in the 8-week waitlist condition might experience worsening of symptoms during this time due to the progression of symptoms or factors such as an unexpected life event. The study team will be able to detect this in the participant’s 4-week and 8-week questionnaires. The study team will contact the participant and conduct a risk assessment if they detect an increase in risk from baseline. If it is deemed that the participant would benefit from immediate assessment or treatment from a mental health service, then the study team will withdraw the participant from the trial and refer them to the relevant support service.

### Strategies to improve adherence to intervention/comparator protocols {15c}

#### For participants

Participants will be regularly contacted by members of the research team to ensure they are completing measures and attending calls. All participants will receive a welcome call after being randomised to ensure they understand the next steps of the trial and to allow for any questions to be answered. Participants will be compensated with an electronic voucher for each assessment they complete. For participants who are eligible to take part in the trial, they will receive their e-vouchers after completing their second assessment 8 weeks post-random allocation to reduce attrition and improve data completeness.

#### For coaches

Coaches will receive weekly online individual or group supervision to facilitate fidelity to the SHAPE intervention. All coaches will have completed a 1-day SHAPE training course and have completed two training cases under close supervision. Coaches will have access to a SHAPE information pack that contains information on the SHAPE treatment tools, worksheets for each tool to give to participants, trial inclusion and exclusion criteria, the trial procedure, the safeguarding protocol, and answers to frequently asked questions. Coaches will also have access to the online modules that accompany the SHAPE intervention tools that they can use to refresh their learning and understanding of the core tools used in SHAPE. Finally, coaches will complete a coach log after each call which asks for the duration of the call, the tools covered in the call, and the duration of administration and planning involved for each call to evaluate compliance and length of time.

#### For assessors

All assessors received training to conduct the SCID-5 for PTSD and MDD by the trial lead or lead clinical psychologist. All assessors administering the SCID-5 telephone assessment will have a script to follow before and after administering the two standardised SCID-5 modules to allow for telephone assessments to be consistent and standardised and to reduce possible assessment effects. All telephone assessments will be recorded, and 10% of the assessments will be double coded to assess for inter-rater reliability. In addition, the first five telephone assessments conducted by each assessor will be double coded by the lead researcher to ensure accuracy and consistency in their initial assessments. Assessors need to accurately diagnose PTSD and MDD in five consecutive calls in order to continue to conduct blind assessments during the trial. A total of 10% of remaining assessments will be chosen at random over the course of the trial.

If the lead researcher is unsure about a diagnosis made by an assessor, they will consult with one of the lead clinical psychologists on the trial who will listen to the recording to confirm the final diagnosis. For assessments where a participant accidentally discloses information revealing what condition they were assigned to, this information will be removed from the recording, and the assessment will be re-rated by another blind assessor.

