## Intervention and comparator

### Intervention and comparator description {15a}

#### SHAPE condition

After screening, assessment, and randomisation, participants randomly allocated to the intervention condition will receive the SHAPE intervention over a period of 8 weeks. SHAPE will be delivered remotely over the telephone or via audio link through Microsoft Teams, dependent on participant preference to further enhance the accessibility of SHAPE coaching and reduce potential barriers (e.g. limited access to the internet or to an electronic device, difficulties with computer literacy). Participants will receive approximately 6 coaching calls (1 call per week) with the expectation that participants or coaches may need to skip a week (due to sickness, annual leave, holidays, etc.). In circumstances where additional clinical support is warranted and would be in the participant’s clinical best interests, up to 2 more sessions can be offered (e.g. prolonged exposure to multiple traumatic events, new trauma that emerges during treatment, an ongoing court case). Coaching calls will last between 30 and 50 min and will focus on a specific tool (as outlined in Table 2).

**Table 2 Tab2:** Tools typically used in SHAPE weekly coaching calls

Core tools
1. THEN vs. NOW for re-experiencing symptoms
2. IF THEN plans for rumination
3. Planning ahead for low mood and avoidance
4. Surveys and behavioural experiments for updating unhelpful thoughts
5. Imagery to create a sense of continuity in the present with what has been lost in the past
6. Responsibility pie charts for guilt and self-blame
7. Realistic risk and worry diary for worry
8. Blueprint for beating stress and low mood

During supervision, coaches will plan their future coaching calls with their designated supervisor, who will be a clinical psychologist on the SHAPE team. Coaches and supervisors will discuss which tools would be most useful to cover in each call to address the key symptoms endorsed on the weekly PTSD and MDD symptom measures. Table 2 provides a list of the core tools typically used in the SHAPE intervention and the symptoms they target.

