#### SHAPE condition timeline

Participants receiving the SHAPE coaching will be sent the PCL-5 and PHQ-9 at the end of each week to assess for changes in symptoms of PTSD and MDD respectively and to help in planning the upcoming coaching call. These measures will be sent via a secure online link for participants to complete on a digital device. Participants will need to enter their unique ID number before completing the self-report measures to allow the research team to link IDs to responses. Halfway through the intervention, participants will receive a longer set of measures to complete. Eight weeks after randomisation, participants will complete a longer set of post-intervention questionnaires and have another SCID-5 telephone assessment to re-assess for PTSD and MDD. Six months after receiving the SHAPE intervention, a final set of follow-up questionnaires will be sent, and participants will have a final remote SCID-5 telephone assessment to re-assess for PTSD and MDD. All post-randomisation SCID-5 assessments will be conducted by blinded assessors, unaware of the participant's allocation.

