#### Implementation {23}

The independent researcher linked to the trial will generate the allocation sequence and randomly assign participants to conditions. They will have access to a condition assignment table that other members of the research team will not be able to access, apart from the lead researcher (JL), until data collection has concluded and all participants have completed the intervention or waitlist condition. The lead researcher will be notified once a participant has been randomised and will inform the participant and their assigned coach of this outcome.

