## Blinding

### Who will be blinded after assignment to interventions {24a}

Participants and coaches will not be blind to treatment allocation due to the nature of the intervention. Assessors conducting the SCID-5 assessment for treatment outcome will be blind at all post-randomisation assessment timepoints. Members of the trial steering committee will also be blind for the duration of the trial until all data analyses have been completed.

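### An unblinded lead researcher may choose which SCID-5 diagnoses are reopened for a final ruling, so the query step on the primary outcome is not protected by the stated blinding

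*Protocol article*

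**What the plan says.** **Outcome.** "The primary outcome measure will be SCID-5 diagnosed PTSD and MDD at 8 weeks post-random allocation" (Main trial analyses, Primary outcome). It is coded present or absent for each participant.

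**Blinding claim.** Who will be blinded {24a}: "Assessors conducting the SCID-5 assessment for treatment outcome will be blind at all post-randomisation assessment timepoints". SHAPE condition timeline: "All post-randomisation SCID-5 assessments will be conducted by blinded assessors". Trial design {12} says the same of the 8-week and 6-month assessments.

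**Who knows the arm.** Implementation {23} says the independent researcher holds "a condition assignment table that other members of the research team will not be able to access, apart from the lead researcher", and continues: "The lead researcher will be notified once a participant has been randomised and will inform the participant and their assigned coach of this outcome". Participants and coaches are unblinded by design.

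**Query rule.** For assessors, under {15c}: "If the lead researcher is unsure about a diagnosis made by an assessor, they will consult with one of the lead clinical psychologists". The psychologist then hears the recorded call, and this review serves to confirm which diagnosis is final. The same section has the lead researcher second-code the first five calls of each assessor. It separately provides that, when a participant lets the allocation slip, the cue is cut from the recording and another blind assessor re-rates it.

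**Supervision.** The SHAPE condition section says coaches plan their calls with "their designated supervisor, who will be a clinical psychologist on the SHAPE team".

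**The concern.** Participants and coaches know the arm and the comparator is a waitlist, so blind rating of the diagnostic interview is the main protection of the primary endpoint. That protection requires the analysed diagnosis, and not only the first one recorded, to be independent of allocation.

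The query rule lets someone who knows the arm decide which diagnoses look doubtful. No objective trigger is set, so knowledge of the arm could influence that choice without anyone intending it. If unexpected diagnoses are queried more often in one arm than in the other, the recovery difference can shift in either direction.

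**Working it through.** The core check is a side-by-side reading. The arithmetic only gives scale.

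**1. Is the person who raises queries blind?** No. Allocation concealment mechanism {22} and Implementation {23} have the lead researcher told of each allocation and passing it on. Section {24a} lists assessors and steering committee members as blind and does not list the lead researcher.

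**2. Does the query rule reach outcome assessments?** Nothing limits it to baseline. The sentence that follows it deals with participants disclosing their condition, which can happen only after randomisation. The section therefore covers post-randomisation ratings, and the query rule carries no exception for them.

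**3. Is the person who settles the query required to be blind?** No such requirement is stated. Implementation {23} withholds the assignment table from other team members until data collection ends. However, coach supervisors are clinical psychologists on the team, and the protocol does not keep the two roles apart for a given participant.

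**4. Does a blind psychologist cure it?** Not fully. If an unblinded person selects the cases, even blind rulings fall on a set of cases that may differ by arm.

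**5. Plan's own figure.** Sample size {19}: recovery 50% against 16%, 90% power, alpha 0.05 (taken as two-sided), 1:1. With mean proportion 0.33,

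n = [1.960·√(2·0.33·0.67) + 1.282·√(0.50·0.50 + 0.16·0.84)]² / 0.34² = (1.303 + 0.795)² / 0.1156 ≈ 38.1, rounded up to 39 per arm.

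39 / 0.85 = 45.9, rounded up to 46 per arm, N = 92. This reproduces the stated figures, which are not in question.

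**6. Scale of one change.** 1/39 = 2.6 percentage points of an arm's recovery rate; 1/46 = 2.2.

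**7. Illustration with assumed rates.** Suppose there is no true effect (16% recovery in both arms, 39 per arm) and a fraction f of the non-recovered SHAPE participants is changed to recovered, with no change in the waitlist arm. Apparent SHAPE recovery is 0.16 + 0.84·f. Simulated two-sided rejection rates, unadjusted two-proportion test at 0.05, 200,000 replicates:

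| f (assumed) | Apparent SHAPE recovery | Rejection rate |
|---|---|---|
| 0 | 16.0% | 5% |
| 5% | 20.2% | 8% |
| 10% | 24.4% | 15% |
| 15% | 28.6% | 27% |

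The documents give no value for f. The table shows how sensitive the test is to one-sided reclassification; it does not estimate what will happen.

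**The case against.** **The outcome is still rated blind.** This stands in part. A blind assessor conducts and first rates each post-randomisation interview, and {24a} claims blinding for assessors, not for the lead researcher. A reader might infer that the primary outcome as a whole is unblinded. The documents do not support that; the gap is confined to the query and final-diagnosis step.

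**The psychologist may not know the arm.** This stands. A reader might infer from the supervision arrangement that the adjudicator knows who is being coached. The protocol refers to more than one lead clinical psychologist and nowhere says that the adjudicator supervises that participant's coach. It supports only that the psychologist is not stated to be blind and that overlap is possible.

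**The rule may be meant for training or eligibility.** It follows text on double-coding and assessor accuracy, so this is a plausible intention. The wording does not impose the limit, and the next sentence concerns post-randomisation assessments. If that was the intention, one added phrase would settle it.

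**Confirming is not changing, and the unseen analysis plan may say which rating is analysed.** That is possible. But a ruling described as settling the final diagnosis would ordinarily be the one analysed, and the protocol does not say otherwise.

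**One diagnosis need not decide the trial.** This stands. A reader might point to a flip in significance: with 39 per arm, 14 against 6 recovered gives p = 0.038 and 13 against 6 gives p = 0.065 (uncorrected chi-square). That is a chosen borderline case. Fisher's exact test already gives 0.068 for 14 against 6. Near the planned effect a single change decides nothing (20 against 6, p = 0.0008; 19 against 6, p = 0.0016). The planned analysis is covariate-adjusted logistic regression. The flip shows that borderline results are fragile and does not measure bias.

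**Conclusion.** The concern holds for the query step. As written, a person who knows every allocation can select primary-outcome diagnoses for review, with no trigger, and the reviewer need not be blind or separate from that participant's coaching supervision. This undercuts the blinding stated in {12}, {24a} and the SHAPE condition timeline.

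The size and direction of any bias are unknown because the frequency of use is not given. Each changed diagnosis is worth 2.6 points at 39 analysed per arm, and the simulated rejection rates rest on assumed, one-directional reclassification. The conclusion assumes that the rule applies after randomisation, as its unrestricted wording allows, and that the confirmed diagnosis is the one analysed.

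**What to change.** **Rule.** For post-randomisation SCID-5 assessments, have doubtful diagnoses raised and settled only by people blind to allocation. Use the route already in the For assessors section: remove arm cues and have another blind assessor re-rate the recording. Use the lead researcher's double-coding for reliability only.

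**Data already collected.** Log by arm every outcome diagnosis changed through the lead-researcher and psychologist route. Have those cases re-rated blind from the recordings, or use the original blind rating. Report a sensitivity analysis on the original blind ratings. Making the uncorrected original rating primary in every case is not necessary, since it would discard legitimate correction of rating errors.

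**Timing.** Data management {26} has recordings deleted once participants have finished and their data are analysed, so the re-rating must come first. Recruitment is complete and data collection was due to finish by December 2025.

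**If not done.** State the exception in {24a} and in the SHAPE condition timeline.

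**Cost.** A short wording change, retrieval of the rating sheets, and a small amount of re-rating by existing assessors. No new participants or measurements are needed.
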